#### Secondary outcomes

##### Objective sleep quality

In addition to estimating our primary outcome of sleep efficiency, we will use the MW8 and MotionWare software to estimate different parameters of sleep quality including: sleep duration (total time spent sleeping), sleep latency (time between “lights out” and falling asleep), and fragmentation index. Briefly, fragmentation index is defined by MotionWare as the sum of (1) the total time spent sleeping categorized as mobile in the epoch-by-epoch mobile/immobile categorization expressed as a percentage of the time spent asleep and (2) the number of immobile bouts that were ≤ 1 min in length expressed as a percentage of the total number of immobile bouts during time spent sleeping. The MW8 provides validated estimates for measures of sleep quality for the following indices: sleep duration, efficiency, fragmentation, and latency [50, 57].

##### Subjective sleep quality

We will also use the PSQI as a measure of subjective sleep quality [47]. This 19-item questionnaire assesses sleep quality using subjective ratings based on the summation of 7 different component scores (i.e., sleep quality, sleep latency, sleep duration, habitual sleep efficiency, sleep disturbance, use of sleeping medication, and daytime dysfunction). Respondents will be asked to answer the questionnaire retrospectively, surveying sleep components spanning the previous month.

##### Cognitive function

We will use a comprehensive neuropsychological battery to examine changes in cognitive function including (1) the 13-item Alzheimer’s Disease Assessment Scale [58], (2) Trail Making (parts A and B) [59]; (3) the Digit Symbol Substitution Test [60]; and (4) category fluency (i.e., vegetables) [60].

### Treatment allocation

#### Randomization

Participants will be randomly assigned (1:1) to either the INT or the waitlist control group (CON). We will use permuted blocks of varying size to ensure balance over time. To ensure concealment of the treatment allocation, the randomization sequences will be generated and held by a central web-based randomization service.

#### Allocation concealment

Recruitment and enrollment of participants will be managed by the research coordinator who will screen for study eligibility, obtain informed consent, and conduct baseline assessment. Following completion of baseline assessment, the research coordinator will access the web-based randomization service and the participant will be assigned a participant number and allocated to the INT or the CON group. Research personnel performing the outcome assessment and data analysis will be blinded to group allocation. We will not be able to blind participants or personnel delivering the interventions to group allocation.

### Experimental groups

#### Personalized chronotherapy group (INT)

Participants allocated to the INT group will receive four once-weekly general sleep hygiene education classes, followed by 20 weeks of (1) individually timed BLT based on the participant’s sleep profile and (2) individually tailored PA promotion.

##### General sleep hygiene education

Following baseline assessment, participants in the INT group will receive a 4-week general sleep hygiene education course (weeks 1–4; 1×/week; 2 h/session). These courses will provide participants with an understanding of (1) how sleep is regulated; (2) the relationship between sleep and cognition; (3) how sleep changes as we age; and (4) why preserving sleep quality is fundamental to healthy aging. Participants will learn strategies to protect sleep including the importance of individually timed BLT (i.e., seek bright light exposure during the day, while avoiding light at night) and regular PA.

At the completion of the 4-week sleep hygiene education course, INT group participants will receive 20 weeks of (1) individually timed BLT based on the participant’s sleep profile and (2) individually tailored PA promotion.

##### Individually timed bright light therapy (BLT)

In week 5, participants in the INT group will meet with a trained research assistant to develop a daily BLT schedule designed to improve sleep quality and address sleep complaints. Using the results from the STOP-BANG questionnaire, we will first counsel participants with moderate-to-high risk of sleep apnea to see a physician. The participant will then work with the research assistant to determine the best regularly scheduled bed time and wake time in order for the participant to dedicate 8 h to sleeping each night (i.e., sleep window). Using the results from the MW8 sleep recordings (i.e., the participant’s current sleep window), and the participant’s recommended sleep window, we will classify participants as (1) phase advanced (falls asleep earlier than intended); (2) phase delayed (falls asleep later than intended or wakes up later than intended); or (3) phase neutral (falls asleep when intended). Participants will then be provided with a commercially available BLT device (Philips goLITE BLU) and be provided a personalized BLT schedule based on their phase classification. The goLITE BLU emits short-wave blue light (~ 200 lx), which possesses greater phase-shifting properties than the rest of the visible light spectrum [61–64]. All BLT doses will be 1 h in duration, twice daily for 20 weeks (i.e., week 5–24). The time and dose-dependent effects of BLT have been well-described elsewhere [65–69].

**Phase advanced:** Participants will be counseled to use BLT 2 h after waking, and again 11 h later (e.g., morning BLT dose, 8:00–9:00 a.m.; evening BLT dose, 7:00–8:00 p.m.). Participants will be instructed to avoid light 1.5 h before sleep window onset. Participants can otherwise continue their normal light routine at night.

**Phase delayed:** Participants will be counseled to use BLT 30 min after waking, and again 11 h later. Participants will be counseled to avoid all light 3 h before sleep window onset.

**Phase neutral:** participants with a neutral sleep phase will be further sub-categorized based on their current waking routine.

Participants who wake up earlier than intended will be counseled to use BLT 2 h after waking, and again 11 h later. Participants will be counseled to avoid light 1.5 h before sleep window onset. Participants can otherwise continue their normal light routine at night.Participants who wake up when intended will be counseled to use BLT 1 h after waking, and again 11 h later. Participants will be instructed to avoid light beginning 2 h before sleep window onset. Participants can otherwise continue their normal light routine at night.

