### Eligibility

#### Inclusion criteria

We will include community-dwelling men and women who (1) are aged between 65 and 85 years and are living in their own home; (2) have preserved general cognition as indicated by a Mini-Mental State Examination (MMSE [45]) score ≥ 24/30; (3) have a baseline Montreal Cognitive Assessment (MoCA [46]) score < 26/30; (4) do not have dementia of any type; (5) do not have any significant impairment in daily function; (6) are currently experiencing poor sleep quality as indicated by a Pittsburgh Sleep Quality Index (PSQI [47]) score > 5; (7) scored < 5/15 on the 15-item Geriatric Depression Scale [48, 49]; (8) are able to walk independently and are in sufficient health to participate in regular PA as indicated by the PAR-Q [44]; and (9) understand, speak, and read English with acceptable visual and auditory acuity.

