#### Exclusion criteria

We will exclude individuals who are (1) diagnosed with obstructive sleep apnea; (2) receiving continuous positive air pressure (CPAP) treatment; (3) at high risk for cardiac complications during PA or unable to self-regulate activity or to understand recommended PA level; and (4) have clinically important peripheral neuropathy or severe musculoskeletal or joint disease that impairs mobility.

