### Measurements

Baseline measurements will be obtained prior to randomization. There will be three measurement sessions: baseline, 12 weeks, and 24 weeks.

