#### Descriptors

We will measure height using a wall-mounted stadiometer and measure weight using a calibrated digital scale. General health and socioeconomic status will be ascertained by questionnaire. In addition, we will survey participants at baseline for obstructive sleep apnea risk using the Snoring, Tiredness, Observed apnea, Blood pressure, Body mass index, Age, Neck circumference and Gender (STOP-BANG) questionnaire [54].

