#### Waitlist group (CON)

Participants in the CON group will receive access to four optional weekly health enrichment lectures during weeks 1–4 of the intervention period. These lectures will provide educational material for participants on healthy weight management, diet, mindful meditation, and goal setting. This group will not receive specific information on PA during these lectures. During weeks 5–24, participants will not receive any intervention and will go about their usual activity. After 6 months follow up, CON participants will receive (1) the sleep hygiene education course and (2) PA counseling and a Fitbit® Flex™.

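### As written, sleep-apnea risk is collected from everyone before randomization, but advice to see a physician is described only for the intervention arm: a minor asymmetry that is cheap to remove

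*Protocol article*

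**What the plan says.** **Collection.** The Descriptors section says "we will survey participants at baseline for obstructive sleep apnea risk", using STOP-BANG and with no restriction to one arm. The Measurements section says "Baseline measurements will be obtained prior to randomization". Allocation concealment confirms the order: "Following completion of baseline assessment, the research coordinator will access the web-based randomization service".

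**Use in INT.** The section on individually timed bright light therapy opens with "In week 5, participants in the INT group will meet with a trained research assistant" to plan the light schedule. It continues, on the STOP-BANG result, "we will first counsel participants with moderate-to-high risk of sleep apnea to see a physician". The participant and the research assistant then go on to set the sleep window.

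**Use in CON.** The Waitlist group section lists optional lectures in weeks 1–4 on weight management, diet, meditation and goal setting. For weeks 5–24 it says "participants will not receive any intervention and will go about their usual activity". After follow-up CON is offered the sleep hygiene course, activity counseling and a tracker. Apnea advice is not mentioned at any stage.

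**Eligibility.** The apnea-related exclusions are "1) diagnosed with obstructive sleep apnea; (2) receiving continuous positive air pressure (CPAP) treatment". Entry also requires that participants "are currently experiencing poor sleep quality as indicated by a Pittsburgh Sleep Quality Index", with a score above 5.

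**Components under test.** The Background and the INT section name three: timed light, tailored activity promotion and general sleep hygiene education.

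**The concern.** People with undiagnosed apnea can enter either arm, and the plan itself expects some participants to be at moderate-to-high risk. If only INT participants are told to see a physician, then only INT has a trial-prompted route to apnea work-up or treatment before the 24-week assessment. The trial excludes people who already have that diagnosis or treatment, so its designers evidently regard both as relevant to the question.

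Two things are at stake. The first is attribution: part of any gain in sleep efficiency could come from apnea care and be credited to chronotherapy. The second is equal handling: a health risk that was collected before allocation would be acted on according to the arm drawn. The second holds even if the effect on sleep efficiency is zero.

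Light, activity promotion and education have to differ between the arms because they are what is being tested. The referral does not.

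**Working it through.** **Step 1: the two arms side by side.**

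| | INT | CON |
|---|---|---|
| STOP-BANG at baseline, before allocation | yes | yes |
| Weeks 1–4 | sleep hygiene classes | optional lectures on other topics |
| Week 5 | planning meeting, with physician advice if at risk | none |
| Weeks 5–24 | light and activity promotion | no intervention |
| After follow-up | – | sleep hygiene course, activity counseling, tracker |
| Physician advice described | yes, week 5 | not at any point |

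Could the word for participants in the referral sentence cover both arms? The sentence before it restricts the meeting to INT, and the sentence after it continues the same meeting with the research assistant. The natural reading is INT only.

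**Step 2: timing.** From week 5 to the 24-week assessment is about 24 − 5 = 19 weeks, which leaves room for a work-up. From week 5 to the 12-week assessment is about 12 − 5 = 7 weeks, so little could reach that outcome.

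**Step 3: possible size.** The article states no figure on this point, so there is none to reproduce. It gives 48 per group and a design effect of 0.50 (Sample size calculation). The share at risk, the share of those treated in time and the effect of treatment are all assumptions.

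Shift in the INT mean (SD units) = share at risk × share of those treated in time × effect in the treated.

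Per net extra treated person among 48:
- effect 0: 0/48 = 0
- effect 0.5 SD: 0.5/48 = 0.0104 SD, and 0.0104/0.50 = 2.1% of the design effect
- effect 1.0 SD: 1.0/48 = 0.0208 SD, or 4.2%

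| Assumed inputs | INT participants treated | Shift | Share of 0.50 |
|---|---|---|---|
| 0.30 × 0.10 × 0 | 48 × 0.03 = 1.4 | 0 | 0% |
| 0.45 × 0.20 × 0.5 | 48 × 0.09 = 4.3 | 0.045 SD | 9% |
| 0.60 × 0.30 × 1.0 | 48 × 0.18 = 8.6 | 0.18 SD | 36% |

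The last row needs all three inputs at their extremes and is unlikely. If CON sought treatment unprompted at half the INT rate, the shifts halve to 0, 0.0225 and 0.09 SD.

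A second set of assumptions (at risk 0.3–0.7, treated 0.1–0.5, effect 0.2–0.5 SD) gives 0.3 × 0.1 × 0.2 = 0.006 SD up to 0.7 × 0.5 × 0.5 = 0.175 SD. Both ranges are wide because the inputs are guesses.

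**Step 4: who can still be handled uniformly.** At the status date of 1 October 2017, 38 of 96 had been recruited. That leaves 96 − 38 = 58, and about 38/2 = 19 per arm already in under 1:1 allocation.

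**The case against.** The strongest counter-argument is that this is a condensed article. Nothing in it says that at-risk CON participants go unadvised. Feedback of screening results is the kind of detail that a full protocol or ethics submission may hold, and ethics approval is stated. This stands in part. A reader might infer that CON participants are knowingly left without advice, and the article does not support that. It does, however, positively place the advice inside one arm's procedure, which goes beyond silence.

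A second objection is that the advice can be read as part of the delivered package. The trial compares a multimodal program with a waitlist, so no gain can be assigned to any single ingredient in any case. This also stands in part. A reader might infer that the primary comparison is biased or its error rate inflated. That does not follow: analysis by allocation remains a valid test of everything INT received. What differs is the package as delivered from the package as named.

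Third, every magnitude input is assumed, and nothing in the article shows that apnea work-up changes actigraphic sleep efficiency within the follow-up. This stands in full. The percentages above cannot carry the case, and even the direction of any effect is not established.

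Fourth, a late remedy is not entirely clean, because early enrollees would be handled differently. This stands, and is counted as a cost of the fix.

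**Conclusion.** The point holds as a minor, cheap improvement. On the article's wording, apnea risk is collected from everyone before allocation, while physician advice is described for INT only and lies outside the three named components. The intention-to-treat contrast and type I error remain valid. The effect on sleep efficiency is probably small and cannot be derived from the document; it could be zero. The case rests on clean attribution, equal handling of a known health risk and a very low cost, not on a demonstrated bias. It assumes that the full protocol does not already provide the same advice to CON. If it does, only the description needs correcting.

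**What to change.** 1. Give the STOP-BANG advice to every participant at moderate-to-high risk at the end of baseline assessment, before allocation, and take it out of the INT-only week-5 meeting. Placing it after the baseline actigraphy leaves the baseline measurement undisturbed. If the full protocol already advises CON, say so instead.
2. For CON participants already enrolled, have unblinded staff such as the research coordinator, who handles allocation, give the advice. Blinded outcome assessors should not do this, because giving it to CON alone would reveal the arm.
3. In both arms, record any new apnea diagnosis or treatment at existing contacts, asked in the same way, and report counts by arm descriptively.
4. Leave the primary analysis unchanged.

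The cost is a one-paragraph amendment and one added question. There are two downsides. Early enrollees (about 19 per arm at the status date; current enrollment is not known) are handled slightly differently from later ones. Some CON participants may also seek apnea care during follow-up, although for later enrollees the prompt would then be the same in both arms. Sample size and the tested intervention are unaffected.

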##### Individually tailored physical activity (PA) promotion

INT group participants will also meet with a certified fitness professional (i.e., the coach) in week 5 to review their current PA level, and develop an individualized PA plan. We will use the brief action planning approach to help participants develop their individualized PA plan [70]. Briefly, this approach requires the coach to guide participants to (1) set an activity goal; (2) develop an action plan; (3) identify barriers and solutions; and then (4) rate their confidence in the plan. This process will be repeated until the confidence rating reaches > 7/10, indicating that the person is confident about implementing the plan. Participants will be counseled to engage in PA at least 4 h before their regularly scheduled bed time.

Participants will then be provided a Fitbit® Flex™ to be worn on the non-dominant wrist 24 h/day—except during water-based activity or when charging the device. The Fitbit® Flex™ is one of the most common wireless PA trackers in the consumer market and is capable of collecting PA data, uploading it to the web, and producing simple graphs and charts of an individual’s activity. PA data from the device will be wirelessly synchronized with the Fitbit online Dashboard, which can be viewed only by the participants and their fitness professional. During weeks 5–24, the fitness professional will review the individual’s PA on the Dashboard and progressively modify the activity goals during nine bi-weekly phone calls.

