#### Primary outcome

We will measure sleep efficiency using the MW8. Briefly, the MW8 is a uni-axial, lightweight, wrist-worn accelerometer designed to observe acceleration ranging in magnitude from 0.01 to 8 G, with a frequency of 3–11 Hz. The filtered acceleration signal is digitized and the magnitude is summed over a user-specified time interval, or “epoch”. At the end of each interval, the summed value or activity “count” is stored in memory and the integrator is reset. Estimates of sleep quality parameters can then be extracted from the device based on the number of counts for a given epoch. For the present study, we will use 60-s epochs, which is consistent with current guidelines for estimating sleep quality [55].

Participants will first be fitted with the MW8 on the non-dominant wrist and provided detailed information on its features (i.e., the light sensor, event marker button, and status indicator). Participants will be instructed to press the event marker button each night when they start trying to sleep, and again each morning when they are finished trying to sleep. We will also provide participants with the Consensus Sleep Diary (CSD)—which they will be asked to complete upon awakening each morning [56]. After wearing the MW8 continuously for at least 14 days, participants will return the MW8 and completed CSD. We will subsequently download and analyze the MW8 data using MotionWare software 1.0.27 (CamNtech). The responses from the CSD will be used to confirm sleep windows identified by participants (as determined by time-stamped event markers). In cases where the event marker and CSD entries disagree for the start time of the sleep window, we will use the light sensor data to determine “lights out”. Similarly, when the event marker and CSD entry disagree for the end of the sleep window, we will use “lights on” and activity onset to determine the end of the sleep window. The MotionWare software will be used to estimate sleep efficiency (i.e., time asleep expressed as a percentage of time in bed).

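### The MotionWatch8 and, in the intervention arm only from week 5, the Fitbit are assigned to the same wrist, which creates an avoidable risk of differential measurement of the primary outcome

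*Protocol article*

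**What the plan says.** All references are to the Protocol article.

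- **Outcome device.** Under Primary outcome: "Participants will first be fitted with the MW8 on the non-dominant wrist". The device is returned "After wearing the MW8 continuously for at least 14 days". Sleep is scored from activity counts per epoch. The MW8 light sensor helps to settle the sleep window when event marker and diary disagree.
- **Intervention device.** Under Individually tailored physical activity (PA) promotion, INT participants receive a Fitbit Flex at the week-5 meeting, "to be worn on the non-dominant wrist 24 h/day". The stated exceptions are "except during water-based activity or when charging the device". The tracker stays in use through coaching: "During weeks 5–24, the fitness professional will review the individual’s PA on the Dashboard".
- **Control arm.** Under Waitlist group (CON): "During weeks 5–24, participants will not receive any intervention and will go about their usual activity". Then: "After 6 months follow up, CON participants will receive (1) the sleep hygiene education course and (2) PA counseling". The same sentence adds the Fitbit to that later package.
- **Visits.** Under Measurements, sessions are at baseline (before randomization), 12 weeks and 24 weeks.
- **Blinding.** Under Allocation concealment: "Research personnel performing the outcome assessment and data analysis will be blinded to group allocation".

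**The concern.** The two wear instructions collide on one wrist, and they do so in one arm only. MW8 recording is not among the exceptions to Fitbit wear. An INT participant who follows both instructions has two bands on the wrist from which the primary outcome is derived. One who finds this uncomfortable may move or remove either device. A CON participant faces none of this.

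At stake is comparability of the recording itself. A second band could displace the MW8 or shade its light sensor. If the participant moves the MW8 to the other wrist, the recording site changes from baseline. Sleep efficiency and the secondary MW8 measures (duration, latency, fragmentation) all come from this one recording.

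**Working it through.** No figure in the plan depends on this point, so the check is mainly a comparison of sections.

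**Step 1. Who wears what, when.** Inputs: Fitbit period weeks 5–24 in INT; no Fitbit in CON until after follow-up; MW8 recording of at least 14 days (2 weeks). The article does not say whether the 14 days run up to a session or start at it, so both are shown.

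| Session | Recording window (14 days before / after) | INT wrist as instructed | CON wrist |
|---|---|---|---|
| Baseline | before randomization | MW8 | MW8 |
| 12 weeks | weeks 10–12 / 12–14 | MW8 + Fitbit either way | MW8 |
| 24 weeks | weeks 22–24 / 24–26 | MW8 + Fitbit if before; unstated if after | MW8 |

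Overlap at 12 weeks follows from the text. At 24 weeks it depends on timing that is not given, and on whether the Fitbit is still worn after week 24. The sample size section powers the trial for the end of the intervention, so the certain overlap is not at the powered time point.

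**Step 2. Can the model separate the two effects?** Statistical analyses specifies fixed effects for group, categorical time and their interaction, with a random intercept. A device effect that is zero at baseline, zero in CON and non-zero in INT after baseline has the same pattern as the treatment effect in the interaction term. Nothing else in the model distinguishes them.

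**Step 3. How large would an artefact have to be to matter?** The document gives no size, so the shift *b* below is purely an assumption, in units of the single-visit SD. Plan inputs: 40 per group, two-sided alpha 0.05, effect size 0.50, correlation 0.88 between adjacent time points. The recruitment figure reproduces: 40 / (1 − 0.15) = 47.06, rounded up to 48 per group, 96 in total.

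SE = s × √(2/40) = s × 0.2236, where s is the SD of the analysed contrast:

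- (a) 24-week values alone: s = 1, SE = 0.224
- (b) change from baseline, correlation decaying to 0.88² = 0.7744: s = √(2 × 0.2256) = 0.672, SE = 0.150
- (c) change from baseline, correlation 0.88 throughout: s = √(2 × 0.12) = 0.490, SE = 0.110

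False-positive rate with no true effect = Φ(−1.96 + b/SE) + Φ(−1.96 − b/SE). Power for a true 0.50 when the artefact works against INT = Φ((0.50 − b)/SE − 1.96).

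| Assumed b (SD) | False-positive rate (a) / (b) / (c) | Power (a) / (b) / (c) |
|---|---|---|
| 0 | 0.05 / 0.05 / 0.05 | 0.61 / 0.91 / 0.995 |
| 0.05 | 0.06 / 0.06 / 0.07 | 0.52 / 0.85 / 0.98 |
| 0.10 | 0.07 / 0.10 / 0.15 | 0.43 / 0.76 / 0.96 |
| 0.20 | 0.15 / 0.27 / 0.45 | 0.27 / 0.52 / 0.78 |

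The plan's stated power of 0.85 lies between (a) and (b) and is matched by none of the three at b = 0. That is a separate matter. The table shows only that, under (b) or (c), a shift of 0.10 SD would raise the false-positive rate to 0.10 or 0.15. It does not show that such a shift occurs.

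**The case against.** The strongest reply is that no artefact has been shown. Two bands on a still wrist have no evident reason to produce counts, and a knock requires wrist movement that the MW8 would register anyway. The light sensor is consulted only when event marker and diary disagree, so shading matters on some nights only. This stands. It limits the point to a risk.

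A reader might infer more than the article supports in four ways:

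- **That the primary result is biased, or biased in a known direction.** Spurious counts would lower INT sleep efficiency and so work against the intervention. A displaced or relocated watch has no sign that can be read from the document. Neither size nor direction can be claimed.
- **That both follow-up recordings are affected.** Only the 12-week overlap is certain.
- **That same-wrist placement breaks the assessors' blinding.** A Fitbit on either wrist would be a cue to allocation. That is a separate, minor matter.
- **That the Fitbit should be taken off for each recording.** It is a component of the intervention, and setting it aside for 14 days would suspend that component while its effect is being measured.

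It can also be said that a condensed article may leave recording-week instructions to a fuller protocol. That would answer an omission. Here the article states both placements, the wear time and a list of exceptions, and these conflict as written. A fuller document may already resolve the conflict, in which case only the published text needs correcting.

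**Conclusion.** The concern holds as an avoidable risk of differential measurement. As written, INT is told to wear two devices on the primary-outcome wrist at the 12-week recording, and at 24 weeks if the recording overlaps Fitbit wear. CON, and both arms at baseline, wear the MW8 alone. Any resulting device effect would be indistinguishable from treatment in the planned group-by-time contrast.

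The size and direction of such an effect cannot be estimated from the document. The table above rests on assumed shifts and should not be read as an estimate. The conclusion itself assumes only that participants follow the two wear instructions as stated, or depart from them by moving one device. It is worth correcting because the outcome concerned is the primary one, the planned analysis cannot repair it, and the correction is nearly free.

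**What to change.** Reconcile Primary outcome with Individually tailored physical activity (PA) promotion. State that during every MW8 recording the MW8 stays on the non-dominant wrist in both arms, that INT participants wear the Fitbit on the other wrist for that period, and that the wrist used for each device is logged. State also whether the 24-week recording runs before or after the end of week 24.

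This removes the collision on the outcome wrist without interrupting the intervention. INT still wears one device more than CON, but not on the wrist being measured. The cost is one instruction and one log entry per recording. Fitbit activity data from those weeks come from the other wrist and may not be fully comparable with other weeks. Because the Fitbit stays in use, the two-week follow-up rule for absent activity data needs no exception.

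At the reported status date 38 of 96 participants had been recruited, so 58 (96 − 38) were still to come and the change could protect most recordings. Recordings made before the change should be identifiable in the data.

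Separately, asking INT participants to take the Fitbit off before contact with blinded assessors would protect the blinding that the article promises.
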